## **Summary**

### **Research title**

The role of genetic predisposition in the effect of green tea on fat oxidation and energy expenditure are

### **Background**

Recent epidemiological studies have suggested that the effect of green tea on fat oxidation and energy expenditure might differ because of differences in the genetic predisposition. This may largely be caused by allele frequencies of relevant polymorphisms that play a major role within the subjects. The effect of green tea is induced by a combination of active components of green tea, the catechins that inhibit the enzyme catechol-O-methyl transferase (COMT) and caffeine that inhibits the enzyme phosphodiesterase (PDE). COMT normally degrades norepinephrin and PDE degrades cAMP. Both increase sympathetic nervous system activity, which will occur continuously after the inhibition of both enzymes thereby resulting in an elevated fat oxidation and energy expenditure. For COMT, three polymorphisms are known from which the *Val/Val* polymorphism codes for the COMTH allele, the thermo stabile enzyme with high activity; the *Met/Met* polymorphism codes for the COMTL allele, the thermo labile enzyme with low activity; and the *Val/Met* polymorphism that codes for the COMTH/L allele, the enzyme with intermediary activity.

Asians appear to be mainly predisposed for the COMTH allele (approximately 75%). From the Caucasians only a minority possesses this polymorphism (25%) since the majority is predisposed with the COMTH/L allele (50%). Therefore, the success rate for lowering body weight through the effect of green tea on fat oxidation and energy expenditure might be increased in Asians compared with Caucasians.

### **Objective**

Investigating the role of genetic predisposition in the effect of green tea on:

- (i) energy expenditure and substrate metabolism
- (ii) hunger and satiety, and energy intake.

### **Study design**

The study has a randomized, crossover design with two conditions. Randomization of the conditions will take place with the help of a digital randomization program.

### **Population**

Forty-eight healthy subjects with a BMI between 18-25 kg/m^2 and aged between 18-50 years from which 24 Caucasians (12 with the COMTH allele and 12 with the COMTL allele) and 24 Asians (12 with the COMTH allele and 12 with the COMTL allele).

### **Outcome parameters**

The outcome of the study will be the effect of green tea on energy expenditure and fat oxidation in subjects that have different COMT polymorphisms, measured in a respiratory chamber. Furthermore, the effect of green tea on hunger and satiety feelings will be determined in the same subjects.

### **Description of the burden and risks for the subjects**

The study contains 2 x 2 test days with a total duration of 72 hours. The subjects will be in the chambers for the total 36 hours stay. There are no risks attached for the subjects while participating in this study.

***Applications***

The outcome of the study can be used for a more individual approach for weight management. Besides green tea more bioactive ingredients that are currently investigated for their weight reducing capabilities may be considered for a specific diet, when their has been established if there are responders and non-responders because of different polymorphisms. Also, it gives an indication whether green tea is an efficient tool for weight management.

## **Introduction**

Overweight and obesity represent a rapidly growing threat to the health of populations in an increasing number of countries [1]. The ultimate cause of obesity is an imbalance between energy intake and energy expenditure (EE)[2]. A negative energy balance is needed to produce weight loss and can be achieved by either decreasing intake or increasing expenditure. Classical weight loss programmes, such as low-fat diets, behavioral modification and exercise, often fail to achieve a long-term maintenance of weight loss [3, 4]. Because of these low success rates, the stimulation of EE (or the prevention of its decline during dieting) by the use of natural herbal nutrients such as green tea and caffeine has attracted interest.

Green tea (GT) is consumed primarily in China, Japan and a few countries in North Africa and the Middle East [5, 6]. Tea is made from the leaves of *Camellia sinensis* L. species of the Theaceae family, GT being the non-oxidised, non-fermented product. As a consequence of this, it contains high quantities of several polyphenolic components such as epicatechin, epicatechin gallate, epigallocatechin and, the most abundant and probably the most pharmacologically active, epigallocatechin gallate (EGCG) [7]. From caffeine, that is also present in GT, it has been reported that it has thermogenic effects and can stimulate fat oxidation in vitro, in part via sympathetic activation of the central nervous system [8]. In humans, caffeine has been shown to stimulate thermogenesis and fat oxidation [9-11]. GT extracts, containing caffeine and catechin-polyphenols, have been reported to have an effect on body weight [7, 12] and EE [13, 14]. The fact that GT stimulates thermogenesis cannot be completely attributed to its caffeine content because the thermogenic effect of GT is greater than that of an equivalent amount of caffeine [13]. As GT combines the best of catechins and caffeine, it has already shown in the past to be an interesting thermoactive food ingredient that assists in preventing or treating overweight in normal weight to obese people.

The sympathetic nervous system (SNS) plays an important role in the regulation of energy homeostasis. Catechins inhibit the enzyme catechol-O-methyl transferase (COMT) which usually degrades norepinephrine. Levels of this neurotransmitter rise in the synaptic cleft as it is not degraded anymore. The activity of the SNS increases and via the elevation of adenyl cyclase subsequently levels of cyclic amino mono phosphate (cAMP), and phospho kinase A (PKA) rise. Consequently, glucose uptake is decreased, lipolysis and thereby fat oxidation is stimulated and uncoupling proteins are upregulated resulting in thermogenesis. Caffeine exerts its effect by inhibiting the

enzyme phosphodiesterase (PDE), that usually degrades cAMP to AMP thereby activating the same pathway as the catechins [15]. An additional advantage is that caffeine binds to the A2a receptor, thereby preventing the binding of adenosine, that is able to decrease norepinephrine, to these receptors. The increase in energy expenditure and fat oxidation does not always appear equally clear in all ethnic groups. For instance studies with Asian subjects seem to report more positive results than studies with Caucasian subjects. Recent literature suggests that this may be caused by differences in relevant enzyme activity, causing differences in sensitivity for these ingredients. In that respect Hodgson *et al.* [16] stated that there is a wide variability in flavonoid O-methylation, a major pathway of flavonoid metabolism, by the enzyme COMT. The inter-individual variability of the activity of COMT could vary as much as 3-fold [16]. Moreover, there is evidence that there is a difference in COMT enzyme activity between ethnic groups [17]. Asian populations have a higher frequency of the thermostable, high activity enzyme, COMTH allele (*Val/Val* polymorphism) than the Caucasian populations. The Caucasian populations have a higher frequency of the thermolabile, low activity enzyme, COMTL allele (*Met/Met* polymorphism) [17]. 50% of Caucasians are homozygous for the COMTL allele (25%) and COMTH allele (25%). The other 50% is heterozygous (*Val/Met* polymorphism) [17]. This may explain the difference in sensitivity to interventions with green tea caffeine mixtures, and why, in some studies with Caucasian subjects, no effect was seen after ingestion of green tea.

We hypothesize that subjects (Asian or Caucasian) with the COMTH allele (*Val/Val* polymorphism) respond stronger to the GT treatment than subjects with the COMTL allele (*Met/Met* polymorphism), consequently have an increased EE and that the genetic differences between Asians and Caucasians are responsible for the different outcomes in GT studies with both subjects.

Therefore, the aim of the present study is to reveal whether genetic predisposition plays a role in the effect of green tea on energy expenditure and fat oxidation, by measuring Caucasian as well as Asian subjects with either a high or low activity polymorphism for the enzyme COMT. This study might reveal why green tea has an effect only in certain people and whether it is only a useful method in these people to initiate weight loss or prevent weight gain.

## **Objectives**

The objectives of this study are to determine the effect of the different COMT polymorphisms after ingestion of green tea on energy expenditure and fat oxidation in a respiration chamber when being fed in energy balance.

## **Subjects**

Forty-eight healthy subjects (age 18-50 years and BMI 18-25 kg/m^2) from which 24 Caucasians and 24 Asians, from each ethnicity 12 with a COMTH allele and 12 with a COMTL allele, will be recruited. The subjects will be recruited via advertisements in the University building and in a local newspaper. Subjects have to be in good health, non-smokers, not using medication (except the use of contraceptive), at most moderate alcohol users (persons consuming less than 10 glasses/week) and also people who drink at most one cup of coffee per day. Dulloo et al. and Kovacs et al. showed that the effect of green tea administration was the highest in people who drunk less than 2 cups of coffee per day [13, 18]. During the initial screening 10 ml blood will be drawn from the subjects to determine the polymorphism. We choose to draw blood instead of taking a sample from the mucous membrane of the cheek as the latter results in 10-20% drop-outs during the analysis. This would mean that more subjects have to be screened or that subjects have to be screened more than once, in case the analyses fail which is more aggravating for the subjects than drawing 10 ml blood once. A questionnaire on health, use of medication, smoking behaviour, alcohol consumption and tea and coffee consumption will be completed. The Dutch translation of the Three Factor Eating Questionnaire (TFEQ) will be used to determine eating behaviour [19, 20]. Non-restrained eaters (<9 times factor 1), these are persons who are not consciously occupied with food and who are caloric restricted, will be selected.

## **Study design**

The study will have a randomized, single-blinded, cross-over design. Randomization takes place using a computerized randomization program. Only the subjects are blinded, as the researcher has to supply the subjects with the treatment. Blinding the researcher as well is not possible because there is no option to check afterwards which capsule the subjects consumed.

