### **Sample size**

The primary parameter is total energy expenditure. Dulloo *et al.* [13] report TEE values of  $9867 \pm 488$  kJ/day and  $9538 \pm 521$  kJ/day for green tea vs placebo [13]. With an  $\alpha$  of 0.05 and  $\beta$  of 0.10 (power=1- $\beta$ =0.90) the number of subjects needed is:

$$N = 21 \times (SD)^2 / (\text{mean1} - \text{mean2})^2 + 0.96$$

$$N = 21 \times (488)^2 / (9867 - 9538)^2 + 0.96$$

$$= 47 \text{ subjects needed}$$

Rounded up, 48 subjects will be included in the experiment which means that each group contains 12 subjects. When taking drop outs into account 193 persons need to be screened. For the Asians with the COMTH allele 17 people have to be screened to get 12 subjects, as the allele frequency is 70%. The allele frequency for the COMTL allele is 15%, which means that 80 people have to be screened. In Caucasians for either the COMTL allele as well as for the COMTH allele 48 people have to be screened, as the allele frequencies are 25%. In total this would mean that 193 subjects have to be screened in order to find 48 subjects. This is an obtainable number since habitual high coffee drinkers do not apply for entering the study as the poster and advertisements mention the inclusion criteria. Also, coffee consumption in Asian people is rather low compared with Caucasians.

An ANOVA repeated measures with post-hoc tests will be used to compare the effects of green tea on TEE and fat oxidation in subjects with different ethnicity and different COMT polymorphisms. A p-value <0.05 will be regarded as statistically significant.

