#### Protocol

Subjects will visit the university twice and during each visit they will stay in the respiration chamber for two days and nights (36hrs). During one of these visits subjects will test the treatment condition (green tea; 757 mg/capsule [84.5 mg EGCG + 2.1 mg caffeine], 3 capsules with each breakfast and dinner) and the other visit they will test the placebo condition (soy oil; 757 mg/capsule, 3 capsules with each breakfast and dinner). Subjects receive a glass of water in order to swallow the capsules more comfortably. Both visits are separated by a period of 4 weeks, which will prevent influences of the previous experiment and influences of differences in menstrual cycle phase on energy expenditure. The respiration chamber experiment starts in the evening of day 1 at 19:00h and ends at 07:00h on day 3.

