### **Statistics**

The average of each group in each of the 2 conditions (green tea or placebo) is calculated for:

- Mm VAS at each time-point; the area under the curve (AUC) is calculated for hunger, satiety, fullness, thirst, desire to eat, time of desire of next meal. This is done with the trapezoid method.
- Conditions are compared using 4-factor ANOVA repeated measures with post-hoc tests to discriminate between groups, and will show possible differences in satiety and energy expenditure. To double-check the outcomes, paired sample T-tests will be performed as well.
- Comparison implies the clinical outcome parameters as mentioned in the paragraph above.
- All results will be visualized in graphs and tables for better understanding.

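### Visit order is not tied to the four COMT-by-ethnicity cells of 12, and period is not named in the analysis, so a visit effect would cost precision in the genotype contrast.

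*Protocol*

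**What the plan says.** The Summary describes the design: "The study has a randomized, crossover design with two conditions". Every subject takes both conditions, so visit order is the only thing randomised. On how this is done, the Summary has "Randomization of the conditions will take place with the help of a digital randomization program" and the main Study design section has "Randomization takes place using a computerized randomization program". Neither mentions strata, blocks or an equal split of the two orders.

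The Sample size section arrives at 48 subjects, "which means that each group contains 12 subjects". The groups are the four combinations of COMT type (high or low activity) and ethnicity. COMT type is determined from blood drawn at screening.

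The analysis is described twice. Sample size has a repeated-measures ANOVA to "compare the effects of green tea on TEE and fat oxidation in subjects with different ethnicity and different COMT polymorphisms". Statistics has "Conditions are compared using 4-factor ANOVA repeated measures with post-hoc tests to discriminate between groups", without listing the four factors, and adds: "To double-check the outcomes, paired sample T-tests will be performed as well".

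On visit effects, the Protocol subsection of Methods and measurements says: "Both visits are separated by a period of 4 weeks, which will prevent influences of the previous experiment". The same sentence also gives menstrual cycle phase as a reason for the interval.

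**The concern.** The main hypothesis, at the end of the Introduction, is that COMT-H subjects respond more strongly to green tea than COMT-L subjects. The test is a between-group comparison of within-subject differences (green tea minus placebo), with 24 subjects on each side, or 12 within one ethnicity.

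Suppose energy expenditure differs between the first and second chamber stay for any reason unrelated to treatment. Each subject's difference then moves up or down by that visit effect, depending on which condition came second. If the mix of orders differs between genotype groups, part of the visit effect enters the genotype contrast. If the mix is the same, nothing enters, but an unmodelled visit effect still sits in the residual and widens the standard error.

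The four-week gap is directed at carry-over and menstrual phase. It does not deal with a general difference between a first and a second stay. Whether such a difference exists, and how large it is, the protocol does not say.

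**Working it through.** **Inputs from the protocol.** Cells of 12, four cells, 24 v 24 for COMT; planning difference 9867 − 9538 = 329 kJ/day; SD 488 kJ/day; significance level 0.05; power 0.90 (all from Sample size).

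**Inputs assumed, because the protocol gives neither.**
- Visit effect π (visit 2 minus visit 1): 100 to 329 kJ/day. The upper end equals the whole planning effect and is taken as an extreme.
- SD of within-subject differences: 345 kJ/day, which is 488 × √(2 × (1 − 0.75)), so a within-subject correlation of 0.75. The alternative of 488 corresponds to a correlation of 0.5. The simulations use 300 and 488.
- Simple 1:1 randomisation of order, wherever chance splits are quoted.

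**The plan's own figure.** 21 × 488² / 329² + 0.96 = 47.16, given as 47 and rounded up to 48. It reproduces, and this point does not affect it.

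**Chance splits in a cell of 12.**
- P(6:6) = 924/4096 = 22.6%.
- P(8:4 or worse) = 2 × 794/4096 = 38.8%.
- P(at least one of four cells 8:4 or worse) = 1 − (1 − 0.388)⁴ = 86%.

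**Leak without a period term.** A subject's difference is shifted by +π if green tea comes second and by −π if it comes first.
- Shift in a cell mean: π × (number second − number first)/12. At 8:4 this is π × 4/12 = π/3.
- COMT contrast, 24 v 24: mean 0, SD = π × √(1/24 + 1/24) = 0.289π. For π = 100 this is 29 kJ/day; for π = 329 it is 95 kJ/day.
- COMT contrast within one ethnicity, 12 v 12: SD = π × √(1/12 + 1/12) = 0.41π.

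**Standard error with balanced order but no period term.** Inflation ≈ √(SD² + π²)/SD.

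| SD of differences | π = 100 | π = 329 |
|---|---|---|
| 345 | 1.04 | 1.38 |
| 488 | 1.02 | 1.21 |

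**Simulation of the COMT contrast** (48 subjects, model for within-subject differences; visit effect 0 to 300; true genotype difference 0 or 329 kJ/day).

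| Order and model | Type I error | Power, SD 300 | Power, SD 488 |
|---|---|---|---|
| Simple, no period | 0.049–0.053 | 0.96 falling to 0.75 | 0.62 falling to 0.50 |
| Simple, period | 0.045–0.053 | 0.96 | 0.61–0.63 |
| 6:6, no period | down to 0.005 (SD 300) or 0.020 (SD 488) | 0.96 falling to 0.80 | 0.62 falling to 0.48 |
| 6:6, period | 0.047–0.051 | 0.96 | 0.62–0.63 |

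The falls occur as the visit effect goes from 0 to 300. Nearly all the lost power comes back with the period term. Balance makes the leak exactly zero even in an unadjusted comparison, but without the period term it leaves the test conservative.

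**The case against.** **The protocol does not say that order is unbalanced.** This stands. A computerised program may use blocks or strata, and silence is not a decision to use simple randomisation. The chance-split figures therefore hold only under the stated assumption. Blocking over the whole sample would still not balance the cells.

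**Period may already be in the model.** This also stands. Treatment, COMT and ethnicity account for three of the four factors. The fourth could be period or order, or it could be time, since the same section analyses appetite scores by time-point. A reader might infer that period is left out; the document does not show that. A statistical analysis plan, not at hand, may define the model. It could supply a period term, but it could not rebalance order after allocation.

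**A reader might infer false positives or systematic bias.** The calculations do not support this. Over repeated allocations the leak averages zero and type I error stays near 0.05. Only conditionally on a marked imbalance does it rise: with green-tea-second counts differing by 6 between the COMT groups and an assumed visit effect of 300, to roughly 10% to 15%. A difference of 6 or more has an 11% chance under simple randomisation.

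**The visit effect is hypothetical.** The protocol gives no evidence for one. At 100 kJ/day the loss is small.

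**The paired t-tests are secondary.** They compare green tea with placebo and do not estimate the genotype contrast. But a check that omits period shares any visit-order error in the cell it tests and cannot expose it.

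**Conclusion.** The point holds as a cheap improvement to the design. The protocol does not tie visit order to the four cells on which its main hypothesis rests, names no period term, and offers as a double-check a test that cannot remove a visit effect.

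The size depends on quantities the protocol does not give. For an assumed visit effect of 100 to 329 kJ/day and allocation without strata, the chance leak into the COMT contrast has SD of about 29 to 95 kJ/day, against a planning effect of 329. With balanced order and no period term, the standard error rises by about 4% to 38% at an assumed SD of 345, or 2% to 21% at 488. If the visit effect is negligible, so is the harm. The documents do not support going further and saying that order is in fact unbalanced, that period is in fact excluded, or that every visit difference reaches the genotype contrast.

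**What to change.** 1. State that visit order is randomised in permuted blocks within each COMT-by-ethnicity cell, aiming at 6 green tea first and 6 placebo first. Each subject's cell is known from screening, so this needs no new information.
2. List the four ANOVA factors, and include period as a named term in the primary TEE model. Sequence in the model for within-subject differences is equivalent.
3. Do not present the unadjusted paired t-tests as confirmation of the ANOVA.

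The cost is one setting in the randomisation program and one degree of freedom (43 instead of 44 for the residual in a four-cell model of 48 differences). If only one change is possible, the period term recovers most of the precision. The cell-wise balance has to be set before allocation starts.

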#### Energy intake

During their stay in the chamber subjects will be fed in energy balance. Subjects receive their breakfast, lunch and dinner, at regular time points. The energy content of the food will be calculated using the equation of Harris-Benedict [30] that calculates Basal Metabolic Rate (BMR). BMR will be multiplied by an activity index of 1.35. Energy intake will be divided over the meals as 20% for breakfast, 40% for lunch, and 40% for dinner. The macronutrient composition of the diet will be 12/55/33 En% (protein/carbohydrate/fat). The diet will consist of normal food products, available in the supermarket. The actual diet will be determined in consultation with the subjects. They can indicate which food products they dislike and based on this information a diet will be composed with the abovementioned macronutrient composition. All foods will be prepared in a research kitchen from the Department of Human Biology by one of the researchers.

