#### Information about capsules

The product information for the green tea capsules can be found in the attachments.

For the placebo capsules there is no direct product information available, the product information from Gelkaps is used for placebo and green tea capsules. When specifying the placebo capsules the green tea extract is replaced with soy oil. The placebo thereby consists for 100% of soy oil. Soy oil is a globally consumed plant oil, and often used as a food additive and has hardly any flavour. Lecithin, which is also present in very small amounts in the capsules, is a product of soy oil after processing. It works as an emulsifier. These capsules have already been used in a previous study (NL19702.068.07/ MEC 07-3-080) and been approved by the medical ethical committee.

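### The reason given for leaving the researcher unblinded is not valid: coded capsule packs, or at least coded data processing, would remove an avoidable source of bias

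*Protocol*

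**What the plan says.** The Study design section of the protocol declares the blinding level openly: "The study will have a randomized, single-blinded, cross-over design". It gives two reasons for stopping at the subject. The first is practical: "Only the subjects are blinded, as the researcher has to supply the subjects with the treatment". The second is stated as an impossibility: "Blinding the researcher as well is not possible because there is no option to check afterwards which capsule the subjects consumed". The same paragraph gives the source of the allocation: "Randomization takes place using a computerized randomization program".

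Under Methods and measurements, the Protocol subsection describes the two conditions as "green tea; 757 mg/capsule [84.5 mg EGCG + 2.1 mg caffeine], 3 capsules with each breakfast and dinner" and "soy oil; 757 mg/capsule, 3 capsules with each breakfast and dinner". The section on the capsules adds: "When specifying the placebo capsules the green tea extract is replaced with soy oil". On meals, the Energy intake section states: "All foods will be prepared in a research kitchen from the Department of Human Biology by one of the researchers".

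The Ethics section sets up subject numbers, with the key held by the researcher and the supervisor, and provides an independent doctor. Nowhere does the protocol mention coded packs, a holder of the allocation list outside the study team, a blinded assessor or a blinded analyst.

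**The concern.** The protocol presents single-blinding as forced, and the argument for that does not work. A design limitation accepted for a wrong reason can usually be removed, so it deserves a second look before the study starts.

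What is at stake is differential handling of the two visits. Each subject is compared with himself or herself, so anything that staff do differently on green tea and placebo days enters the contrast directly. The hypothesis in the Introduction is directional: stronger response in the high-activity genotype. Hunger and satiety are named endpoints and rest on hourly self-ratings. Total energy expenditure includes activity, which can respond to encouragement and contact. Choices about excluding or repeating data could also be made with the condition known.

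**Working it through.** No figure in the plan is in dispute. The check sets the two stated reasons against the rest of the protocol and then traces where knowledge of the condition could act.

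**Reason 1: the researcher hands out the treatment.** Handing out a container does not require knowing its contents. If the container carries only a subject number and a visit number, the researcher can do this task blind.

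**Reason 2: nobody can check later what was swallowed.** Identity is fixed by two records: the computer-generated list (subject, visit, condition) and the label of the pack issued. If a third person holds the list, the condition can be recovered after the data are locked. An unblinded researcher has no better check. If the capsules look alike, that researcher too relies on the container label. Neither reason therefore rules out blinding.

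**Is the material suitable?** The two conditions match in capsule weight (757 mg), in number (3) and in the meals at which they are taken. The placebo is the same product with the extract replaced. The protocol does not state that the capsules look and smell the same. Its own blinding of subjects, who meet both types, presumes something close to it.

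**Where could knowledge of the condition act?**

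| Outcome or step | Exposed? | Basis in the protocol |
|---|---|---|
| Gas concentrations | Hardly | Sampling and processing are computerised (Indirect calorimetry) |
| Total energy expenditure | Through subject activity | Activity is one of its three components (Energy expenditure and substrate oxidation) |
| Appetite scores | Yes, though the raters are blinded subjects | Hourly self-ratings (Questionnaires) |
| Meals | Partly | Prepared by a researcher, but with energy, meal split and macronutrients set by formula (Energy intake) |
| Data exclusions and derivation | Possible | No blinded processor is named |

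**Can the derivation of the components move the primary parameter?** The protocol defines DEE = RMR − SMR and AEE = 24-h EE − RMR. Adding the parts gives SMR + (RMR − SMR) + (24-h EE − RMR) = 24-h EE. SMR and RMR cancel, so the choice of sleeping window or regression line redistributes the total but cannot change it.

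**Scale of the target.** From the Sample size section, 9867 − 9538 = 329 kJ/day, and 329 / 9538 = 3.4% of the placebo value. This is the size of the effect sought. It is not an estimate of bias.

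**Workload of coding.** 48 subjects × 2 visits = 96 subject-visits.

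**The case against.** The strongest reply is that the protocol is honest about being single-blind and that its main safeguards are sound: randomized order, within-subject comparison, blinded subjects and an automated measurement of the primary parameter. Diet is constrained by formula. With two subjects in the chambers, no researcher is present at night. The text does not say that one person supplies capsules, cooks, instructs subjects, collects appetite scores and derives the values. Only capsule supply and meal preparation are assigned to researchers, and not necessarily to the same one. All of this stands, and it keeps the point moderate.

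It is also fair that the capsules are not stated to be indistinguishable. A researcher who handles both types repeatedly may notice a difference that a subject, seeing them four weeks apart, would miss. Coded packs would then fail to blind the researcher, so the remedy must be conditional.

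A reader might infer two stronger things. One is that an unblinded choice of the sleeping window or radar regression could by itself produce the 329 kJ/day effect. It cannot: those steps only partition the total, and SMR is defined by a fixed rule. The other is that genotype should be sealed from the start. Genotype decides eligibility and fills four cells of 12, so the team needs it during recruitment.

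What the reply does not rescue is the claim of impossibility, or the absence of any blinded step after capsule supply.

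**Conclusion.** The stated justification is invalid and nothing else in the protocol repairs it. Calling the study single-blind is accurate; the error is the claim that nothing more can be done. The consequence is avoidable exposure of subject contact and activity, appetite scores and data handling to knowledge of the condition. The appetite scores and the components of expenditure are more exposed than total energy expenditure, which is reached mainly through activity.

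The size of any bias cannot be computed from the document. The conclusion that identity can be recovered needs only an allocation list and pack labels. The conclusion that the researcher can be fully blinded rests on a further assumption, that the capsules cannot be told apart by someone who handles both. The protocol does not confirm this. The change is worth making because it is specific and cheap, not because a bias has been shown.

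**What to change.** 1. Delete the sentence stating that the researcher cannot be blinded.
2. Have the capsule supplier, or an existing staff member with no contact with subjects or data, label each visit's capsules with subject and visit number only. Record the pack issued at each visit.
3. Keep the allocation list with that person, sealed until energy expenditure, substrate oxidation, SMR, DEE, AEE and appetite AUC values are locked. Give the independent doctor already named under Ethics emergency access.
4. Before the first visit, confirm whether a researcher can tell the two capsules apart. If not, describe the study as double-blinded.
5. If they can be told apart, keep the single-blind description and have data processed and analysed under coded condition labels (A/B), with the key held outside that work.

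The cost is packing and list-keeping for 96 subject-visits and the agreement of the supplier or an uninvolved colleague. Subjects face no added procedure, and recruitment by genotype is unaffected.
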